#### Patient identification and screening

Patients introduced to any of the participating sites with an acute ACL injury will be assessed for eligibility. In habitual practice, patients who might have an ACL injury often present themselves at the emergency care unit and/or are referred to either (1) the Department of Physical Medicine and Rehabilitation or (2) the Orthopaedic Department. The screening and identification strategy will be performed similarly.

Like usual practice, during the initial consultation (V0), a physical examination of the knee including clinical tests to diagnose ACL injuries and a patient history will be taken by a medical doctor. Based on these findings the speculation of an ACL injury can be supported or rejected. If the clinical tests were positive, an MRI is scheduled to confirm the ACL tear. Additionally, if all other inclusion criteria are checked, the medical doctor will already inform the patient about the possibility to be included in the study.

During the second consultation (V1) with the medical doctor, the findings of the MRI are discussed. If the ACL tear is confirmed, the medical doctor asks if there is interest in participating in the study. If the patient wants to be involved in this study, he/she is referred to the appointed study assistant for further eligibility checks and extra information about the study. If the medical doctor confirms the eligibility and the patient agrees upon participation, informed consent will be signed by both the investigator and the patient.

To optimize recruitment and not miss potential candidates, the study nurse of the participating center will weekly check the planning of both the orthopedic and physical medicine department and remind the medical doctors of all potential candidates. Furthermore, regular contact with the emergency department is necessary to ensure that all relevant patients at the emergency department are correctly referred to either a consultation at the Department of Physical Medicine and Rehabilitation or the Department of Orthopedics.

Screening logs will be implemented at each recruiting site to document the reasons for non-inclusion in the study (e.g., the reason for decline or exclusion).

### Interventions

The study compares two standard treatment options for an acute ACL injury: [1] conservative treatment with optional delayed ACL reconstruction and [2] surgical treatment consisting of immediate ACL reconstruction and rehabilitation. We will not deviate from current practice, except for the randomization, to keep the trial pragmatic. Hence, the study does not predetermine the type of ACL reconstruction and patients will choose their own physiotherapist for the rehabilitation. However, to guarantee a minimum quality of rehabilitation, which is crucial for the integrity of the comparison, we will provide evidence-based guidelines and progression criteria for ACL rehabilitation to the physiotherapists.

#### Conservative treatment consisting of rehabilitation and optional delayed ACL reconstruction

##### Rehabilitation

Patients in this treatment arm will complete rehabilitation with their physiotherapist. As mentioned above, the physiotherapist will receive evidence-based guidelines and criteria for ACL rehabilitation. However, there is enough flexibility in how the physiotherapist wants to apply those guidelines in clinical practice. The guidelines are based on current literature [26–28]. The rehabilitation protocol involves three phases (see below), and progression is based on goal-based criteria, not time based. If the specific goals of the previous phase are achieved, patients can progress to the next phase. We ask the participant to fill in a modified version of the Exercise Adherence Rating Scale (EARS) [29] (see outcomes) to evaluate the quality of the rehabilitation, at every follow-up visit (visit 3–7, see Table 1). The EARS consists of several questions about different exercises performed, the intensity and frequency of the rehabilitation program, and barriers and facilitators for adherence to the predefined exercises.

**Table 1 Tab1:** Overview of the rehabilitation guidelines per treatment arm. *The rehabilitation protocol consists of three phases. Each phase focuses on specific aims and progression criteria are provided to decide on progression to the next phase*

	Rehabilitation + optional delayed surgery	Immediate reconstruction + rehabilitation	Criteria for progression
**Phase 0**: Pre-operative phase	Not applicable	- Restore full knee extension - Activation hamstrings and quadriceps to avoid atrophy - Patient education - Instruction of post-operative exercises	
**Phase 1**: Acute phase	- Restore full knee extension, patella mobility, full flexion ROM - Eliminate effusion - Restore gait pattern - Improve muscle control and activation - Restore proprioception	- Restore full knee extension, patella mobility, start flexion ROM - Eliminate effusion - Restore gait pattern - Improve muscle control and activation - Restore proprioception	- Full passive knee extension, flexion: Active flexion ROM ≥ 115° - Minimal/ no joint effusion - Independent walking - Quadriceps strength 60% of contralateral side
**Phase 2**: Progressive strengthening + neuromuscular control	- Restore full knee ROM - Improve lower extremity muscular strength + endurance - Improve proprioception, balance and neuromuscular control	- Restore full knee ROM - Improve lower extremity muscular strength + endurance - Improve proprioception, balance and neuromuscular control	- Full ROM - Quadriceps strength 80% of contralateral side - Single leg hop test: 80% of contralateral side - No pain or effusion
**Phase 3**: Return to activity/sports	- Normalize lower extremity strength - Improve muscle power + endurance - Perform sport-specific drills - Gradually return to full sport	- Normalize lower extremity strength - Improve muscle power + endurance - Perform sport-specific drills - Gradually return to full sport	- Strength quadriceps + hamstrings > 90% contralateral side - Single leg hop test: >90% contralateral side

#### Indications for delayed surgery

If a patient of the conservative treatment group complains about consistent symptomatic instability of the knee that prevents rehabilitation progression, a delayed surgery can be considered. A positive pivot shift in combination with ACL insufficiency-induced instability and an additional MRI are needed to confirm the cause of instability (Criteria based on the KANON trial [1]). According to current practice, delayed surgery will not be performed within the first 12 weeks post-injury.

#### Immediate ACL reconstruction and rehabilitation

##### ACL reconstructive surgery

We will not impose any guidelines on the type of ACL reconstruction to keep the trial pragmatic. The decision on graft type and surgery technique is a clinical decision made by the orthopedic surgeon of the participating center. All surgery details will be noted in the patient register and can be retrieved if necessary. Although the study does not predetermine the type of surgery, we will impose strict criteria for the timing of the surgery. The immediate ACL reconstruction must be performed within 12 weeks after the ACL injury. This to avoid that patients of the immediate ACL reconstruction already had a considerable amount of pre-operative physiotherapy sessions, thus keeping a clear distinction between both groups.

##### Rehabilitation

The same goal-based rehabilitation protocol will be applied as in the intervention group (see Table 2). However, depending on the type of surgery, some time restrictions regarding range of motion and weight-bearing can be imposed by the surgeon. In that case, the physiotherapist has to slightly adapt the rehabilitation protocol. Rehabilitation starts the first days after surgery. Furthermore, also preoperative rehabilitation sessions can be performed.

**Table 2 Tab2:** Overview trial procedures

Procedures/ Assessment	Screening	Randomisation + baseline assessment	Intervention	Follow-Up Visits				
Visits	V1	V2		V3	V4	V5	V6	V7
Timing (months)	< 8 weeks after injury	Baseline < 8 weeks after injury		4 months post-injury ± 14 days	7 months post-injury ± 14 days	12 months post-injury ± 14 days	24 months post-injury ± 14 days	36 months post-injury ± 14 days
Enrolment								
Eligibility screen	X							
Informed consent	X							
Randomisation		X						
Intervention								
1. Rehabilitation + optional delayed surgery			(X)^1^	(X)^1^	(X)^1^	(X)^1^	(X)^1^	(X)^1^
2. Immediate ACL reconstruction			X^2^					
Assessments								
MRI	(retrieved from patient record)			X				X
PROMS^#^		X		X	X	X	X	X
Adverse events				X	X	X	X	X
Isokinetic strength				X	X	X	X	X
Single leg hop for distance					X	X	X	X

Table 2: *Trial procedures for a single patient*

^*# l*^*the following patient reported outcome measures (PROMS) will be assessed at V2-V7: KOOS, return-to-sport, return-to-work, IPQ-R, TSK, EARS and quality of rehabilitation;*^1^Optional delayed surgery can occur after randomization; ^2^Immediate ACL reconstruction has to be performed within 12 weeks after injury

### Outcomes

#### Primary outcomes

The Knee Injury and Osteoarthritis Outcome Score (KOOS) QOL is the primary outcome of this study. The KOOS collects data on five knee-specific patient-centered outcomes: pain, symptoms, ADL, sport and recreational function (Sport/Rec), and knee-related QOL. Since most ACL patients report no or only small issues with pain, symptoms, and ADL function preoperatively there is less room for improvement on those subscales, and therefore the subscales Sport/Rec and QOL are recommended for follow-up ACL patients [30, 31]. We chose the subscale QOL as the primary outcome since not all participants will be involved in sports, and therefore the Sport/Rec is less useful in our trial. Standardized answer options are given on a Likert scale, and each question is assigned a score from 0 to 4. A normalized score is calculated for each subscale (100 indicating no symptoms and 0 indicating extreme symptoms). Test-retest reliability of the KOOS [32] is high with ICC values between 0.83 and 0.95 for KOOS QOL and between 0.61 and 0.95 for the other subscales. The minimal detectable change is 7-7.2 for the KOOS QOL and between 5 and 12 for the other subscales [32].

#### Secondary outcomes

##### The Knee Injury and Osteoarthritis Outcome Score (KOOS)

subscales: pain, symptoms, ADL, sport and recreational function [22].

##### International Knee Documentation Committee Subjective Knee Form (IKDC subjective)

this questionnaire administers patient’s perception of knee symptoms during activities of daily living and sports activities. This questionnaire consists of 18 items and a total score is calculated (range 0-100, with higher scores representing lower levels of symptoms, higher levels of function and participation) [33].

##### Modified Tegner Score

this scale will be used to grade the activity level of the patients [34]. A score is given from 1 (sick leave or disability pension because of knee problems) to 10 (competitive sports) based on the highest level of activities the patient performs regularly. Beside the current activity level, we will also ask the pre-injury activity level to determine when the patient returned to normal activities.

##### Illness perception questionnaire (IPQ-R)

the illness perceptions questionnaire measures patients’ beliefs and feelings about their illness (such as whether they think the illness can be cured or controlled by their treatment) [35].

##### Tampa Scale for Kinesiophobia

this questionnaire measures the fear of movement. It is a 11 item scale that uses a 4-point likert scale. Psychological factors such as fear of movement might be an important predictor of outcome after ACL injury, regardless of surgical treatment or not. Hartigan et al. (2013) showed for example that kinesiophobia is related to knee function after surgery [36].

##### The EQ-5D-5 L questionnaire

this questionnaire measures generic health status in 5 dimensions: mobility, self-care, usual activities, pain/discomfort and anxiety/depression. Each dimension has 3 levels: no problems, moderate problems and extreme problems. The sum of the score on the 5 dimensions describes the patient’s health state. We will administer this questionnaire for the economic evaluation to compute quality-adjusted life years (QALYs).

##### Functional tests

*The single leg hop for distance.* This functional test assesses knee functional performance. The patient will be asked to jump as far as possible on one leg (push-off and landing on same leg). After the landing, the patient has to keep balance for 3 s without shuffling on the stance leg. The patient will performs 3 trials on the injured leg and 3 trials on the uninjured leg. Subsequently the limb symmetry index (LSI) will be calculated by dividing the distance jumped on the injured leg by the distance jumped on the contralateral, uninjured leg [37]. This test is often used to decide on return-to-sport, with an LSI > 90% as criterium for readiness for return-to-sport [38].

*Isokinetic strength of the quadriceps and hamstrings*. Isokinetic strength of the quadriceps and hamstrings will be measured on an isokinetic dynamometer (Biodex or Cybex). This to assess recovery of strength. For both the quadriceps and hamstrings maximal concentric strength will be measured at 60°/sec and 240°/sec. Similar to the single leg hop for distance, the symmetry between the strength of the injured leg and uninjured leg will be calculated. Again an LSI of > 90% is often used as criterium for readiness for return-to-sport as a score < 90% is correlated with increased risk for re-injury risk after ACL reconstruction [38, 39].

##### Adverse events

Adverse events such as surgical complications, arthrofibrosis, infection and any additional acute injury to the ipsilateral or contralateral knee (such as re-injury, graft-rupture or contralateral ACL injury, laesions of menisci, cartilage or ligament,… ) will be registered at every follow-up visit.

##### Return to work/ return to pre-injury activity level

A customized questionnaire will be developed to administer the following data: days of sick-leave, previous and current occupational level, type of job, job-related activities, pre-injury sport level and time to return to pre-injury activity level.

##### Rehabilitation

A customized questionnaire is developed to collect information about the rehabilitation: the frequency (amount of sessions per week) and intensity of physiotherapy sessions, whether the rehabilitation involved active exercise therapy, the type of exercises and whether the patient performed exercises at home or in the gym. A list of exercises is provided. The patient has to check which exercises were performed during the rehabilitation. and whether the patient performed exercises at home or strength training (in a fitness center).

##### The anterior cruciate ligament OsteoArthritis score (ACLOAS)

This scoring system will be used to score and monitor structural knee joint damage on MRI [40]. The following joint features are assessed with this scoring system: acute osteo-chondral injuries, traumatic and degenerative bone marrow lesions, meniscus morphology and extrusion, osteophytes, collateral and cruciate ligaments including ACL graft, Hoffa-synovitis and effusion-synovitis. In addition to the MRI features assessed with the ACLOAS, the following MRI features will be assessed to detect recovery of the ACL: slope of ACL with respect to the Blumensaat line, distance between the Blumensaat line and the ACL, bounderies and tension of the ACL [16].

##### Central MRI reading

All pseudonymized MRI images will be scored by one central reader. This central reader will be a physician with expertise in musculoskeletal imaging. The central reader scores the images according to ACLOAS.

### Timeline

An overview of all assessments that will be performed at the different study visits can be found in Table 1. Five follow-up visits are planned: at 4 and 7, 12, 24 and 36 months after randomization see Fig. 1.

**Fig. 1 Fig1:**
[figure not shown]
Trial flow chart V1 = visit 1

### Sample size

The outcome(s) on which the sample size calculation is based upon is the KOOS QOL, a self-administered questionnaire. The outcome for the **non-inferiority analysis** is the change on the KOOS QOL between the baseline measurement and 1 year after randomization. The sample size was calculated using the power procedure in SAS 9.4 to show with 80% of power that conservative treatment is not inferior to standard treatment, where a non-inferiority margin of 7 (change-points) was adopted based on the study of Collins et al. who report a minimal detectable change in KOOS QOL of 7 points [33]. The analysis consists in estimating the difference in mean change-scores between both treatment arms with a one-sided 95% confidence interval (Corresponding to a 5% significance level). Non-inferiority will be concluded when the lower limit of the confidence interval will be above the non-inferiority margin of -7. An equal treatment effect in both arms and a standard deviation for the change-score of 19 were assumed for the sample size calculation [1]. Assuming a drop-out of 10%, a total number of 260 patients is required for randomization. For the **superiority analysis** the sample size was calculated to demonstrate with a two-sample t-test a difference between the two treatment groups with respect to the change in KOOS QOL score at 7 months follow-up compared to post-injury. Considering equal group sizes, a two-sided 5% significance level, 90% power, the smallest important difference as 13.5 change-points [31] a standard deviation of 18 for the change in KOOS QOL versus baseline [31], and a 10% drop-out rate, the calculation indicates a total sample size of 88 patients. Furthermore, the 5% significance level was adopted since a hierarchy of statistical testing will be used. Only if the non-inferiority test is significant at 12 months, the test of superiority at 7 months will be performed since superiority is judged necessary to change practice. Furthermore, a prediction model will be built in the intervention group (rehabilitation and optional delayed ACL reconstruction) with the event of delayed surgery as binary outcome and where an initial set of the five predictor variables described above will be considered. Following the rule of thumb of including at least 10 events per parameter in the model, this analysis requires at least 50 events (i.e. delayed surgeries in the experimental group). Assuming that 1/3 of patients in the experimental group will need delayed surgery (KANON Trial), a minimum of 150 patients will be needed in the intervention group in order to develop such a prediction model.

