#### Primary outcome analysis

The primary analysis will compare the intervention group with the control group on their mean change in KOOS QOL at 2 primary endpoints:

Non-inferiority testing at 1 year post-injury.Superiority testing at 7 months post-injury.

A one-sided 95% confidence interval for the mean difference between groups excluding 7 units in the disadvantage of the conservative treatment will be considered as a demonstration of non-inferiority at 1 year. A two-sided 95% confidence interval for the mean difference between groups excluding 13.5 units in the advantage of the conservative treatment will be considered as a demonstration of superiority at 7 months.

Estimation and testing of these mean differences will be based on a single analysis model. A linear model for repeated measurements will be used, applied to outcome measures at all time points, modelling an unstructured residual variance-covariance matrix to deal with correlations due to the longitudinal data structure. Compared to separate cross-sectional analyses, this approach improves the power and minimizes the effects of possible bias due to drop-out. All patients with at least one outcome measurement are included in the analysis, even if they had no outcome measured at 7 or 12 months. The model includes group, time-point and group by time-point interaction as effects. The mean differences between the groups at 7 and 12 months and their confidence intervals will be estimated as post-hoc tests based on this model. Given the hierarchical approach of statistical testing (superiority testing only if non-inferiority is demonstrated), no correction for multiple testing will be performed.

The primary analysis will be applied to the ITT population. Patients without outcome measures apart from baseline will be excluded.

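### The 260 patients do not follow from the stated one-sided 5% non-inferiority inputs, which give about 206; 260 is what one-sided 2.5% would give, so level, power and size need reconciling

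*Protocol article*

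**What the plan says.** The Sample size section of the protocol article gives every input for the non-inferiority comparison at 12 months:

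- Power: the aim is "to show with 80% of power that conservative treatment is not inferior to standard treatment".
- Margin: "a non-inferiority margin of 7 (change-points) was adopted".
- True difference and SD: "An equal treatment effect in both arms and a standard deviation for the change-score of 19 were assumed for the sample size calculation".
- Level: the difference in mean change is estimated "with a one-sided 95% confidence interval (Corresponding to a 5% significance level").
- Software: "The sample size was calculated using the power procedure in SAS 9.4".
- Result: "Assuming a drop-out of 10%, a total number of 260 patients is required for randomization".

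The Primary outcome analysis section repeats the level in the decision rule: "A one-sided 95% confidence interval for the mean difference between groups excluding 7 units in the disadvantage of the conservative treatment" demonstrates non-inferiority.

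The Randomization section takes 130 per arm as the minimum for the primary analysis, so the 260 rests on equal arms. It then plans 130 for immediate reconstruction and 150 for conservative treatment, 280 in all. The 150 comes from the prediction model. The superiority test at 7 months is carried out only if non-inferiority is shown at 12 months.

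**The concern.** All inputs are on the page, so 260 should be reproducible, and it is not. The gap is far beyond rounding, and it closes completely if one input, the significance level, is halved. That leaves it unclear which confidence bound the primary test was designed around.

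This matters because the non-inferiority test is the first confirmatory test and the gate to the second. The two candidate bounds can give different verdicts on the same data. If the published report has a one-sided 95% bound above -7 but a two-sided 95% lower limit below it, a critic could point to the sample size as evidence that the stricter bound was planned. The protocol as written would not settle the argument.

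**Working it through.** **Inputs** (Sample size section): margin 7, SD 19, true difference 0, power 80%, one-sided level 5%, drop-out 10%, equal arms.

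**Step 1. Check the conventions on the protocol's other figure.** The superiority calculation (difference 13.5, SD 18, two-sided 5%, 90% power) needs 39 per arm by the two-sample t-test. 39/0.9 = 43.3, rounded up to 44 per arm, gives 88, as stated. A t-based calculation, with drop-out handled by dividing by 0.9, therefore reproduces the sponsor's figure.

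**Step 2. Stated inputs, one-sided 5%.** Normal approximation, per arm:

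n = 2 × SD² × (z₁₋α + z₁₋β)² / margin² = 2 × 361 × (1.645 + 0.842)² / 49 = 722 × 6.183 / 49 = 91.1, so 92.

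The noncentral t calculation also gives 92 (power 80.1%; 91 gives 79.7%). Total evaluable 184; 184/0.9 = 204.4, so 205 randomised, or 206 if each arm is rounded up (103 per arm). The stated 260 is 260/206 = 1.26 times this.

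**Step 3. Can another convention explain 260?**

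| Variant at one-sided 5% | Randomised |
|---|---|
| 80% power, all drop-out and rounding conventions | 203 to 206 |
| 80% power, allocation 1:1.15 | 206 |
| 85% power | 234 to 238 |
| 90% power | 280 to 284 |

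None gives 260. (The 280 in the last row coincides with planned enrolment, but the Randomization section derives that from 130 + 150.)

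**Step 4. Halve the level to one-sided 2.5%, nothing else changed.** Normal approximation: 722 × (1.960 + 0.842)² / 49 = 722 × 7.849 / 49 = 115.7, so 116. Noncentral t: 116 per arm gives 79.8% and 117 gives 80.1%, so 117. Total 234; 234/0.9 = 260 exactly, which is 130 per arm, the minimum in the Randomization section.

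**Step 5. Other routes to 260 at one-sided 5%.** An SD of about 21.4 (117 per arm by noncentral t), or a true disadvantage of 0.8 points: 722 × 6.183 / 6.2² = 116.1, so 117 per arm. Neither input is stated; the second contradicts the assumption of equal effect.

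**Step 6. Power at the planned size, after 10% drop-out.** SE = 19 × √(1/n₁ + 1/n₂); noncentrality = 7/SE.

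| Randomised | Evaluable | SE | 7/SE | Power, one-sided 5% | Power, one-sided 2.5% |
|---|---|---|---|---|---|
| 260 | 117 + 117 | 2.484 | 2.818 | 87.8% | 80.1% |
| 280 | 117 + 135 | 2.400 | 2.917 | 89.7% | 82.8% |

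**Step 7. Where the two bounds disagree, at 117 + 135.** The one-sided 95% bound clears -7 if the observed difference exceeds -7 + 1.651 × 2.400 = -3.04. The two-sided 95% limit requires more than -7 + 1.970 × 2.400 = -2.27. Observed differences from about -3.0 to -2.3 pass one rule and fail the other. With truly equal arms, 89.7% - 82.8% = 6.9% of trials would land there.

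**The case against.** The strongest reply is that the protocol does not contradict itself on the level. The Sample size and Primary outcome analysis sections both name a one-sided 95% bound, and the former equates it with 5%. One-sided 5% is a declared, prespecified choice, and no passage mentions 2.5% for non-inferiority. A reader might infer from the exact match that the trial was sized at 2.5% and is being tested at twice its design error rate. The match is strong evidence, but an unstated SD or true difference would also yield 260, so the documents do not establish this. That part of the reply stands.

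It is also fair that the error is on the safe side. A reader might infer that the trial is too small; it is not. Enrolment of 260 exceeds the 206 needed at the stated level, and the stated 80% power is met under either level. What fails is the claim that 260 is required for 80% power.

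A third tempting argument sets the 5% gate against 2.5% in the favourable direction for the superiority test. It does not hold for the rule as written. The Primary outcome analysis section requires the two-sided 95% interval to exclude 13.5 points in favour of conservative treatment, so the 2.5% applies at a true difference of 13.5, not at zero.

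What the reply does not do is account for 260. The testing hierarchy, offered as the reason for the 5% level, explains why alpha is not split between two tests. It does not explain a number that the stated level does not produce.

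**Conclusion.** The point holds as an arithmetic inconsistency in the primary gatekeeping test. The stated inputs give about 205 to 206 randomised, not 260. One-sided 2.5% accounts for the figure exactly and is the likeliest explanation, but it remains an inference.

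The practical consequence is uncertainty about the decision bound, which at 280 randomised affects observed differences between about -3.0 and -2.3 points. It is not a shortage of patients.

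The conclusion assumes a t-based calculation with equal arms and drop-out applied by division, as the superiority figure supports. The power figures further assume that the SD of 19 and the 10% drop-out hold, and they use a two-sample comparison. The planned repeated-measures model may be more precise, but that would not explain 260.

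**What to change.** Retrieve the original SAS calculation, establish which level was entered, and reconcile the Sample size and Primary outcome analysis sections before the data are unblinded.

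- **If one-sided 2.5% was used:** amend both sections so that non-inferiority is concluded when the lower limit of the two-sided 95% confidence interval is above -7, state the level as one-sided 2.5%, and keep 260 required and 280 planned. This halves the chance of a false non-inferiority claim at the margin from 5% to 2.5%. The cost is a formal protocol amendment during recruitment, since the confirmatory rule changes, and power of about 83% instead of 90% at 280. That is still above the stated 80%.
- **If one-sided 5% is intended:** keep the rule and correct the sample size statement. Either give the required number as about 206, or give the power as about 88% for 260 and 90% for 280. Enrolment need not change. The cost is a correction to the sample size text.
- **If another input was used** (for example a larger SD): state it, and show that it gives 260.

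No option needs additional patients.
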